### Qualitative research

Semi-structured interviews are conducted to identify determinants which contribute to the safety, clinical effectiveness and cost-effectiveness of hospital ward care by PAs. Also barriers and facilitators for the implementation of PAs in the role of hospitalist are explored. The interviews are held with a sample of PAs, (specialized) MDs, heads of the departments and nurses. Sampling is done purposively. A variety of care providers are include, covering different medical specialties and medical ward care models. Interviews will be taken until data saturation is achieved on the basis of interim-analyses after each set of five to eight interviews, with a minimum of twenty interviews. A topic list, which will be refined iteratively during the process of data collection and analysis, is used to frame the interview. The TICD framework of Flottorp et al is used to standardize the reporting of barriers and facilitators [28]. Barriers are analyzed in the context of the innovation itself, the individual professional and the patient, and the social context, the organizational context and the economic and political context.

### Economic evaluation

To assess the cost implications and efficiency of substitution of hospital ward care from MDs to teams with PAs, an economic evaluation is conducted alongside the outcomes evaluation. This economic evaluation is based on the general principles of a cost-effectiveness analysis, except that the time horizon per included patient is limited to one month after discharge. If equivalence of effects is established the economic decision rule alters in ‘cost minimization’. The primary cost outcome for the economic evaluation is costs associated with the principal admission (LoHS, resource use, consultation of health care suppliers, salaries, productivity loss) and costs that occurred after discharge that is potentially related to hospital ward care (unplanned readmission, presentation at emergency departments, visits of general practitioner, required home care, productivity loss) in a period from admission until one month after discharge (Table 1). The primary effect outcome in the economic evaluation is EQ-5D based QALYs. We will also analyze costs in relation to LoHS, the primary outcome in the outcomes evaluations. Besides these costs and effects, information about patient characteristics such as gender, age, primary diagnoses and co-morbidities are collected in order to account for patient case-mix as far as possible. All patient-related volumes are collected in detail at an individual patient level, primarily from medical patient records and patient and care provider questionnaires. Costs will be calculated by multiplying the volumes of healthcare use with corresponding unit prices, derived from the Dutch Manual for Costing Research [29], which also include organizational overhead costs. All figures will be related to the price level of the same year.

**Table 1 T1:** Volumes included in the economic evaluation

**Volume**	**Unit**
**During hospital stay at the included ward**^ ***** ^	
Length of hospital stay	Number of days
Non-elective transfer to ICU	Number of days
*Resource* use:	
Surgery	Type of surgery
Medication	Frequency, dose and type of medicine
Laboratory tests	Frequency and type of blood test
Radiographic imaging	Frequency and type of radiographic imaging
Scopic tests	Frequency and type of scopic test
Blood components	Number of units
Consultation with health care suppliers^‡^	Number of consultations
*Medical ward staff:*	
Hospitalists	Working hours per week hospitalist
Supervision by medical specialist	Number of hours supervision per week
**During the first month after discharge**^†^	
Non-elective presentation at emergency department after discharge	Number of presentations at emergency department
Non-elective readmission	Number of days
Non-elective visit to GP	Number of visits to GP post
	Number of visits by GP at patient’s home
	Number of visits to GP
	Number of telephone contacts with GP
Required nursing home care	Number of hours per week
Required domestic home care	Number of hours per week
Productivity loss	Hours per week

*Abbreviations*: *ICU* Intensive Care Unit, *GP* General Practitioner.

^*^Assessed by extraction of patient medical records.

^†^Assessed by patient questionnaires one month after discharge.

^‡^e.g. medical specialist, physiotherapist, dietician, diabetes nurse, occupational therapist, medical social work, psychologist.

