### Primary outcome

LoHS is the primary outcome measure. Reducing LoHs is important for payers of healthcare and for many patients. LoHS is defined as the time period in days between date of discharge and date of admission. To control for discharge delay for nonmedical reasons, i.e. delay attributable to waiting times for a place in a nursing home or a rehabilitation clinic, or help in the patient’s own home, we also register the date of completion of medical treatment in the hospital.

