### Secondary outcomes

#### Quality of hospital ward care

To assess the quality of ward care, a set of eleven global clinical and process indicators has been selected from the literature and suggestions by a physician panel. The clinical indicators were derived from a national set of indicators for quality of hospital care from the Dutch Health Care Inspectorate (IGZ) [22]. All indicators cover a period of maximum one month after discharge. The selected indicators are:

Clinical indicators:

• Inhospital mortality

• Unplanned transfer to intensive care unit

• Cardiopulmonary resuscitation

• Pressure sore developed during admission

• Fever: number of days body temperature ≥38

• Pain score: number of days Numeric Rating Score ≥7

• Hospital infections: infusion-, urinary track-, airway-, and postoperative wound infections

• Presentation at department of emergency, within one month after discharge

• Non-elective readmission within one month after discharge

Process indicators:

• Days between discharge and letter of discharge

• Introduction hospitalist to the patient less than 24 hours after hospital admission

Data about unplanned readmission and presentation at emergency department after discharge are collected using self-administered patient questionnaires, which are send at one month after discharge date. Information about the other indicators will be retrospectively derived from patient medical records.

#### **
*Patients health-related quality of life*
**

Generic health-related quality of life is measured with the Euroqol-5D (EQ-5D), which is a widely used validated questionnaire containing five domains: mobility, self-care, usual activities, pain, and anxiety/depression [23]. Each domain has three possible levels indicating; no problems, moderate problems or sever problems. Besides, respondents are asked to value their overall health status on a visual analog scale, ranging from 0 (defined as the worst imaginable health state) to 100 (defined as the best imaginable health state). The EQ-5D is assessed by patient questionnaires at three time points: at admission, discharge and one month after discharge.

#### **
*Patient experiences with medical ward care*
**

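### Post-discharge costs count readmissions and GP contacts only if non-elective and omit outpatient visits, so the cost comparison would favour whichever ward model shifts more planned care past discharge

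*Protocol article*

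**What the plan says.** All references are to the protocol article.

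- **Economic evaluation, text.** The primary cost outcome covers the index admission plus costs up to one month after discharge. The post-discharge part is described as "costs that occurred after discharge that is potentially related to hospital ward care (unplanned readmission, presentation at emergency departments, visits of general practitioner"; the full list in the bracket is "unplanned readmission, presentation at emergency departments, visits of general practitioner, required home care, productivity loss". GP visits carry no restriction here.
- **Table 1.** It is titled "Volumes included in the economic evaluation", so it reads as the list of what is counted, not as examples. Its post-discharge rows are "Non-elective presentation at emergency department after discharge", "Non-elective readmission" (in days), four types of GP contact under "Non-elective visit to GP", nursing and domestic home care, and productivity loss. A footnote says these come from the patient questionnaire one month after discharge.
- **Table 1, during the stay.** Bed days, laboratory tests, imaging, scopic tests, medication and consultations (medical specialists and physiotherapists among them) are all counted.
- **Quality of hospital ward care.** The readmission indicator is "Non-elective readmission within one month after discharge".
- **Primary outcome.** "LoHS is defined as the time period in days between date of discharge and date of admission". The measure covers the index admission only.

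**The concern.** A non-elective filter makes sense for a quality indicator, where an unplanned return signals that something went wrong. A cost measure has a different purpose: it should count the resources used, whether or not they were scheduled. Carried into Table 1, the filter treats the same service differently on either side of the discharge date. A specialist review or scan during the stay is costed; the same service at a scheduled outpatient visit a few days later is not. A bed day in the index stay is costed; a bed day in a planned readmission is not.

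The study hypothesises a shorter stay under the PA/MD model, and bed days saved lower the measured cost. If part of a shorter stay were achieved by scheduling care after discharge, the saving would be counted and some of the replacement care would not. Costs are also to be analysed against length of stay. If effects are found equivalent, the decision rule becomes cost minimisation, and the conclusion then rests on the cost difference alone.

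**Working it through.** **1. What is counted, side by side**

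| Resource | During the stay (Table 1) | Month after discharge, text | Month after discharge, Table 1 |
|---|---|---|---|
| Hospital bed days | all | unplanned readmission | non-elective readmission |
| Specialist and allied-health consultations | all | not listed | not listed |
| Laboratory, imaging, scopic tests | all | not listed | not listed |
| Emergency department | – | listed | non-elective |
| GP contacts | – | listed, no limit | non-elective |
| Home care | – | listed | listed, no limit |
| Productivity loss | listed in the text only | listed | listed, no limit |

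Two results follow. Planned readmissions and outpatient visits are outside the cost outcome in both places. The text and the table disagree on GP visits. Home care is counted with no non-elective limit, so the plan already accepts that arranged care after discharge belongs in the costs.

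**2. Direction of the error**

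Let P be the mean cost per patient of planned contacts left out (planned readmission, planned GP, outpatient). Then

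measured cost difference = full cost difference − (P in PA/MD wards − P in MD wards).

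If P is equal in both arms, the bracket is zero and the difference in mean costs is unbiased. If P is larger in one arm, that arm looks cheaper than it is by the whole bracket. The sign is open: the error can favour either model.

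**3. Can the plan detect a difference in P?**

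No. Planned contacts are not among the cost volumes, the quality indicators or the listed covariables. Discharge destination is a covariable, but it does not record scheduled follow-up.

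**4. Illustration only**

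The plan's target is 20% of 7 days: 0.20 × 7 = 1.4 days. The document gives no rate or length of planned readmission, no outpatient frequency and no unit price. Every other input below is an assumption.

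Uncounted inpatient days per patient = excess share with a planned readmission × its length:

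| Assumed excess share | Assumed length (days) | Uncounted days | Share of 1.4 days |
|---|---|---|---|
| 2% | 2 | 0.02 × 2 = 0.04 | 3% |
| 5% | 4 | 0.05 × 4 = 0.20 | 14% |
| 10% | 7 | 0.10 × 7 = 0.70 | 50% |
| 20% | 7 | 0.20 × 7 = 1.40 | 100% |

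For outpatient visits, suppose one visit costs 0.1 to 0.5 of a ward day. One extra visit per patient then offsets 0.1/1.4 = 7% to 0.5/1.4 = 36% of the value of 1.4 days.

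A span of 3% to 100% shows only that the answer depends on inputs the document does not give. It is not an estimate of the bias.

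**The case against.** **The scope is a stated choice.** Post-discharge costs are restricted to those potentially related to ward care, and a planned readmission can be part of the treatment plan whichever model runs the ward. This is a coherent reading, but it does not cover everything: a check or readmission arranged at discharge can also be related to ward care, and the unfiltered home-care rows show that being planned was not itself a reason for exclusion.

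**Earlier discharge as pure gain.** A reader might infer that days moved out of the ward disappear from outcomes and costs alike. The document does not support that. Home care and productivity loss are costed, emergency presentations and unplanned readmissions catch discharges that go wrong, and the one-month EQ-5D feeds the QALYs. Length of stay is defined for the index admission and is measured correctly as defined.

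**A real difference between arms.** A reader might also infer that PA/MD wards schedule more outpatient follow-up, because hospitalists are asked about hours spent supporting outpatient care. That item is a workload question put to PAs and medical residents alike. It says nothing about follow-up of the study patients or about which arm does more. The hypothesised mechanism is more standardised and continuous care, not a transfer of care past discharge.

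**The remedy has its own risk.** In a non-randomised study with heterogeneous wards, planned visits vary with diagnosis, subspecialty and hospital policy. Adding them could bring in case-mix differences as well as noise. This stands, and it is why adjustment and reporting both ways belong in the fix.

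**The GP mismatch is small.** The text points to Table 1 for detail, so a wording correction is enough.

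**Conclusion.** The gap is real and is stated in the document: Table 1 presents itself as the list of included volumes, so this is not a detail left to a fuller protocol or analysis plan. It concerns the economic evaluation. The bias is conditional: it arises only if planned follow-up or planned readmission differs between the ward models, and then it favours the arm with more of it. The document does not show such a difference, does not indicate its sign, and collects nothing that would reveal it. Part of any shift is captured by items already in the plan. No magnitude can be derived, and the illustrative percentages should not be quoted as findings. The primary estimate and the non-elective quality indicators need no correction. This is a cheap improvement worth making, most of all because the economic conclusion may come to rest on costs alone.

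**What to change.** 1. In the one-month questionnaire and Table 1, record all readmission days, all GP contacts and all hospital outpatient visits, each marked planned or unplanned.
2. Cost them in the economic evaluation with case-mix adjustment, and report the cost results with and without planned contacts.
3. Keep the non-elective restriction for the quality indicators.
4. Report total hospital days from admission to one month after the index discharge (index stay plus any readmission) as a supportive outcome beside length of stay.
5. Make the Economic evaluation text and Table 1 agree on GP visits.

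Cost: a few extra questions in a questionnaire that is already sent, and unit prices for outpatient visits. Routine or diagnosis-driven visits will add noise and some case-mix variation; reporting both versions lets the reader see how much the conclusion depends on them.

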### Confounders

Because of the non-randomized character of this study and the heterogeneity of patients and hospital wards, there is a risk of confounding. We will correct for a number of predefined confounders in the statistical analyses. The covariables related to *patients* are: gender, age, education, ethnicity, marital status, smoking status, body mass index, primary diagnosis, co morbidities, number of prior hospitalizations, type of admission (elective or emergent), discharge destination and the health-related quality of life at admission. *Healthcare provider factors* are gender, age, highest education, profession, years since graduation, years on the job, extent of employment, regularity of work schedules and workload. *Hospital ward characteristics* are medical specialism, hospital type, teaching status, number of admissions, bed occupancy, and number of MDs, PAs and nurses are assessed. Covariables are extracted from patient medical records and patient and care provider questionnaires.

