### Data analyses

To compare hospital wards utilizing a mixed ‘PA/MD model’ with wards utilizing a solely ‘MD model’, we use logistic regression analyses for dichotomous outcomes and linear regression analysis for continuous outcomes, both with random coefficients to account for statistical clustering of data in hospital wards. The analysis is on an intention to treat basis and matching will be taken into account. Missing values are substituted by multiple imputation techniques. Multivariable models are constructed to correct for potential confounders. Covariables are included in the final model only if they modify the regression coefficient of ward care model (i.e. the central determinant) by more than 10% (regardless of statistical significance of effects). Explorative subgroup analyses per medical specialism will be conducted for each set of at least six wards with similar specialism are included. All estimates are calculated with 95% confidence intervals.

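### The post-discharge costs have no volume for days in a nursing home or rehabilitation clinic, so the incremental cost could be biased if the arms differ in institutional discharge

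*Protocol article*

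**What the plan says.** In the protocol article, the Economic evaluation section sets the cost horizon from admission to one month after discharge. It lists the post-discharge costs as "unplanned readmission, presentation at emergency departments, visits of general practitioner, required home care, productivity loss". Table 1 itemises these volumes down to telephone contacts with the general practitioner. Two of its rows concern care: "Required nursing home care" and "Required domestic home care", both in hours per week. The only post-discharge volume in days is non-elective readmission. All post-discharge volumes come from the one-month patient questionnaire.

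Elsewhere the article recognises institutional destinations. Under Primary outcome it names "delay attributable to waiting times for a place in a nursing home or a rehabilitation clinic" as a nonmedical reason for late discharge, and for that reason "we also register the date of completion of medical treatment in the hospital". Under Confounders, "discharge destination" is one of the patient covariables. It is not listed as a costed volume.

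**The concern.** The hypothesised benefit of the PA/MD model is a shorter hospital stay, and length of stay is itself a costed volume. An economic evaluation of such a model should be able to see whether care moved elsewhere. As written, a day in hospital carries a price and a day in a rehabilitation clinic carries none. A day in a nursing home is probably unpriced too.

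The perspective is not confined to the hospital, because domestic help, general-practice contacts and productivity loss are all counted. A narrow perspective therefore does not explain the gap. The stakes rise if effects are judged equivalent: the article then switches to cost minimization, and the cost difference alone decides. Allocation is not randomized, so nothing in the design ensures that the arms have similar discharge destinations.

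**Working it through.** **1. The cost list against the destinations.** No stated figure is at stake here, so the first check is of the text.
- Rehabilitation clinic: named under Primary outcome; absent from the Economic evaluation text and from Table 1.
- Nursing home: named under Primary outcome. In Table 1 the only candidate is "Required nursing home care". Its unit is hours per week, its neighbour is domestic help in the same unit, and the text has one category for both, home care. Nursing at home is the likelier reading, but the article does not say so. If a residential stay was meant, hours per week is not a usable unit for it.
- Date of completed treatment: separates out waiting in hospital for a place. It does not price the place.
- Discharge destination: a covariable subject to the rule "Covariables are included in the final model only if they modify the regression coefficient of ward care model" by more than 10%. Adjusting for it does not price a stay, and it is determined after exposure to the ward model.

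**2. Illustrative size.** From Sample size calculation, the target difference is 20% of 7 days: 0.20 × 7 = 1.4 hospital days. The documents give no discharge shares, institutional stays or day prices, so these are assumptions:
- q, the excess share of patients sent to an institution in the PA/MD arm: 2% to 10%
- d, institutional days within the month: 10 to 30
- r, price of an institutional day relative to a hospital day: 0.25 to 1.0

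Omitted cost per patient = q × d × r, in hospital-day equivalents.
- Lowest: 0.02 × 10 × 0.25 = 0.05
- Highest: 0.10 × 30 × 1.0 = 3.0

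Net saving = 1.4 − q × d × r, other costs being equal. For d = 20:

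| r | q = 2% | q = 5% | q = 10% |
|---|---|---|---|
| 0.25 | 1.30 | 1.15 | 0.90 |
| 0.5 | 1.20 | 0.90 | 0.40 |
| 1.0 | 1.00 | 0.40 | −0.60 |

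The plan would record 1.4 in every cell. The excess share at which the saving vanishes is q = 1.4 / (d × r). For d = 30 this is 18.7% (r = 0.25), 9.3% (r = 0.5) and 4.7% (r = 1.0).

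**3. Earlier discharge to the same destination.** Suppose the arms send equal shares to institutions and PA/MD patients simply leave 1.4 days sooner. The cost window starts at discharge. A stay that lasts the whole month then gives the same institutional days in both arms, a difference of 0. Only stays that end inside the window on a fixed calendar date would add days. If 5% to 15% of all patients had such stays (assumption), that is 0.05 × 1.4 = 0.07 to 0.15 × 1.4 = 0.21 days per patient, before any price ratio. A difference between arms in destination or duration is therefore the larger risk.

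**The case against.** The strongest reply is that incremental cost is biased only if the arms differ in institutional use, since equal use cancels. Nothing in the documents says that the PA/MD model changes where patients go; the stated mechanism is standardisation and continuity of ward care. The timing of institutional discharge is also linked to waiting for a place, which is a nonmedical cause. All of this stands. The concern is a conditional one, and its direction is unknown: if the MD arm used institutions more, the omission would understate the PA/MD saving.

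A reader might infer that a shorter stay is booked as a pure saving. The documents do not support that. Readmission days, emergency visits, general-practice contacts, home care and productivity loss are all priced, and EQ-5D is measured one month after discharge. Discharge destination is recorded, so a shift could be seen, although not priced.

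A reader might also take it as settled that nursing-home stays are left out. That is an inference from the unit and position of one ambiguous row. For rehabilitation clinics no such doubt exists.

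A deliberately narrow scope is possible, because the article limits post-discharge costs to those potentially related to ward care. But transfer to an institution is at least as closely tied to discharge decisions as domestic help, which is included.

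**Conclusion.** The gap is real but conditional. The cost set has no rehabilitation-clinic item and no volume in institutional days, and the nursing-care row needs clarification. If the arms differ in how often or how long patients are discharged to an institution, the incremental cost could be biased, and the plan as written would not price the difference. The documents do not allow the bias to be estimated. Under the assumed ranges it runs from 0.05 to 3.0 hospital-day equivalents per patient, against the 1.4-day target. The upper end needs a 10-point difference in destination, a full 30-day stay and price parity all at once. The stronger statement, that the cost result is biased, is not supported. The length-of-stay analysis itself is unaffected; the point concerns the economic conclusion.

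**What to change.** - State in Table 1 whether "Required nursing home care" means nursing at home or a residential stay.
- Add two post-discharge volumes: days in a nursing home and days in a rehabilitation clinic within the month. Collect them in the existing one-month questionnaire and price them per day.
- Where the questionnaire is missing, impute the days, with recorded discharge destination as a predictor. This fits the multiple imputation already planned. Destination is a category and cannot supply a number of days by itself.
- Report discharge destination by arm.
- Vary institutional days and prices in the one-way sensitivity analyses already planned under Economic analyses. If data collection can no longer change, state the omission and rely on these last two steps.

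The cost is two questionnaire items, two unit prices and a small burden on patients. One limit remains: because the window starts at discharge, the added items will not register an earlier transfer when the institutional stay outlasts the month.

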### Study aim

The primary aim of this study is to determine the effectiveness of hospital ward care by MDs compared to a patient medical care team consisting of both PAs and MDs. It is hypothesized that due to reallocation of care to a fixed number of PAs per hospital ward, inpatient care becomes more standardized and continued resulting in improved care, which will be reflected by shorter hospital stay. To measure effectiveness we therefore choose length of hospital stay (LoHS) as primary outcome measure. Besides the effectiveness, also the effects on quality and continuity of care and patient and care provider experiences are investigated.

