### Economic analyses

Discounting of costs and effects is applied as recommended for health economic evaluations in The Netherlands [29]. A comparison is made between the intervention and control group on incremental costs and incremental effects. The incremental cost-effectiveness ratio (ICER) will be calculated as follows: ICER = (Δ costs/Δ effects) where Δ costs represents the difference in annual mean costs between intervention and control group, and Δ effects represents the difference in QALYs between the two groups.

The uncertainty associated with estimates is explored with a bootstrap resampling procedure to produce cost-effectiveness planes as well as targeted one-way sensitivity analyses of potential drivers of key cost (such as type of ward). The bootstrapped ICERs will be presented in a cost-effective acceptability curve displaying the probability that the intervention is cost-effective for a wide range of willingness-to-pay thresholds. P-value is set at 0.05 to indicate statistical significance. To test for several assumptions (i.e. cost-prices and salary), one-way sensitivity analyses will be conducted on the range of extremes.

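### Economic evaluation: QALYs accrue over length of stay plus one month, so the arm that discharges earlier is credited with fewer QALYs for the same health course

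*Protocol article*

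**What the plan says.** The Economic evaluation section states that "the time horizon per included patient is limited to one month after discharge". It defines the primary cost outcome over "in a period from admission until one month after discharge" and adds: "The primary effect outcome in the economic evaluation is EQ-5D based QALYs". Under Secondary outcomes, the paragraph on health-related quality of life places the EQ-5D "at three time points: at admission, discharge and one month after discharge", so the last utility value for each patient falls a month after that patient's own discharge.

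The Economic analyses section defines the ICER so that "Δ effects represents the difference in QALYs between the two groups". It gives no common end date and does not rescale QALYs for time observed. On the cost side it says that "Δ costs represents the difference in annual mean costs between intervention and control group".

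The Study aim section expects more standardised care, "resulting in improved care, which will be reflected by shorter hospital stay". The sample size section plans for a 20% relative difference on a mean LoHS of 7 days.

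**The concern.** A QALY is utility multiplied by time. Here the time is LoHS plus one month, and LoHS is what the intervention is meant to shorten. Two patients with the same utility on every day since admission get different QALY totals if one goes home sooner. The days cut from the stay drop off the end of the window and in effect count as zero.

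The loss therefore falls on the PA/MD arm exactly when the study hypothesis is true. Because wards are not randomised, a LoHS difference caused by case mix would pass into QALYs by the same route.

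What is at stake is the ICER denominator, the position of the bootstrap cloud on the cost-effectiveness plane, and possibly the rule that switches to cost minimisation if effects are equivalent. QALY differences attainable over about five weeks are small, so a small artefact can matter.

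**Working it through.** The article gives no figure for QALYs or window length to reproduce. The only planning figure used is the LoHS difference.

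**Inputs from the article**
- Mean LoHS 7 days and relative difference 20% (Sample size calculation): 0.20 × 7 = 1.4 days.
- Window per patient: LoHS + 1 month (Economic evaluation, with the EQ-5D time points).

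**Assumptions**
- One month = 30.4 days; one year = 365.25 days.
- Mean utility over the missing days: 0.7, range 0.5 to 0.9. The article gives no utilities.
- QALY = area under the utility curve over the stated window.

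**Window length**
- MD arm: 7 + 30.4 = 37.4 days.
- PA/MD arm: 5.6 + 30.4 = 36.0 days.
- Difference: 1.4 / 37.4 = 3.7% shorter.

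**QALY loss with an identical, constant health course**: −(days missing × utility) / 365.25
- Utility 0.7: −1.4 × 0.7 / 365.25 = −0.0027, against a control total of 37.4 × 0.7 / 365.25 = 0.072.
- Utility 0.5: −1.4 × 0.5 / 365.25 = −0.0019.
- Utility 0.9: −1.4 × 0.9 / 365.25 = −0.0034.
- Utility 0.7, 10% LoHS effect: −0.7 × 0.7 / 365.25 = −0.0013.
- Utility 0.7, 5% LoHS effect: −0.35 × 0.7 / 365.25 = −0.0007.

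An identical linear recovery from 0.5 at admission to 0.8 at day 37.4 (assumed) gives −0.0030. With a fixed 37.4-day window in both arms, an identical course gives exactly 0.

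**Utility gain needed to cancel the loss over the PA/MD window**: 1.4 × 0.7 / 36.0 = 0.027.

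**Equal utilities at the three measurements** (0.5, 0.65 and 0.8, assumed), linear interpolation:
- MD: (7 × 0.575 + 30.4 × 0.725) / 365.25 = 26.065 / 365.25.
- PA/MD, stated window: (5.6 × 0.575 + 30.4 × 0.725) / 365.25 = 25.26 / 365.25; difference −0.805 / 365.25 = −0.0022.
- PA/MD, last value carried to day 37.4: (25.26 + 1.4 × 0.8) / 365.25 = 26.38 / 365.25; difference +0.315 / 365.25 = +0.0009.

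In this example the sign of the QALY difference depends on the window alone.

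**Costs.** Counted from admission, the PA/MD arm is not charged for days 36.0 to 37.4. Any positive daily cost in that interval favours PA/MD. The article prints no unit prices, so this cannot be put in figures.

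**The case against.** The case for leaving the plan alone has four parts.

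1. **The QALY formula is not printed.** The phrase about the period from admission closes the definition of the cost outcome, and a condensed article may leave interpolation, death and rescaling to a fuller plan. A reader might infer that this phrase by itself sets the QALY window. It does not. The QALY window follows from the separate horizon sentence together with the EQ-5D schedule. Those two are stated rules rather than omissions, and nothing shown corrects for unequal time. The reference to annual costs concerns the numerator only and fits poorly with a one-month horizon.

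2. **Anchoring at discharge has a purpose.** It gives both arms equal time at risk of readmission, emergency visits and GP contacts. This stands as a reason to keep that window for those indicators and as a sensitivity analysis. It does not justify unequal time in a QALY total.

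3. **The bias is not net.** A reader might infer that the economic result as a whole is tilted against PA/MD, for example by EUR 27 per patient for every EUR 10,000 of willingness to pay (0.0027 × 10,000). The documents do not support that: the figure is gross, and the uncharged last days pull costs the other way by an unknown amount.

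4. **The remedy is not free on the cost side.** Table 1 records post-discharge use as one-month counts or weekly hours from one questionnaire, with no event dates mentioned. Costs therefore cannot simply be cut or extended at a fixed day. This stands and shapes the fix.

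**Conclusion.** The point holds for the economic evaluation. Followed as written, the QALY window is shorter in the arm that discharges earlier. At the planned effect the resulting loss is about 0.0027 QALY per patient at utility 0.7, and it shrinks in proportion to the LoHS difference. The size rests on assumed utilities and on QALYs being accumulated over the stated window without rescaling. For an identical health course, the direction needs only positive mean utility over the missing days.

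Two stronger readings should be avoided. Spreading the loss over the 30 post-discharge days alone gives a break-even gain of 1.4 × 0.7 / 30 = 0.033, but the PA/MD window is 36 days and the figure is 0.027. Nor does the point touch the study's main conclusion: the LoHS analysis and the sample size do not use QALYs, and the planned analysis of costs in relation to LoHS does not use them either.

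**What to change.** - **QALYs.** Compute them for every patient over one common horizon counted from admission. Interpolate EQ-5D between the three measurements, carry the last value to the common end date, and use 0 after death. Choose the horizon so that few long stays are truncated.
- **Costs.** Put them on the same horizon by apportioning each patient's one-month post-discharge volumes at a constant rate: volume × (horizon − LoHS) / 30.4. State this as an assumption, and reconcile the reference to annual costs in the ICER definition with the chosen horizon.
- **Sensitivity analysis.** Report the discharge-anchored window alongside.

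Cost of the change: the QALY side needs no new data, since the EQ-5D values and the admission and discharge dates are already collected. The price is some carry-forward for short stays, some truncation for long ones, and the apportioning assumption for costs. A patient whose stay exceeds the horizon would contribute no post-discharge costs, and a longer horizon means more carry-forward for short stays. The choice of horizon should therefore be fixed and justified before the data are analysed.
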